### Setting, participants and eligibility criteria

This study is open to randomized controlled multi-arm trials (Phase II-IV) comparing the effects of pharmacological treatments with antipsychotics to placebo (primary outcome) or any comparator (sensitivity analysis). Individual trial size is not an eligibility criterion. Eligible trials will include adult participants diagnosed with schizophrenia, schizoaffective or schizophreniform disorders. Trials must include PANSS and/or BPRS individual participant data at baseline and outcome. Studies meeting the criteria described in
Table 1 have been requested from
vivli.org (Vivli) and
yoda.yale.edu (YODA Project). Requested studies from the YODA Project are solely sponsored by Johnson & Johnson. In addition, Vivli provides data from the following sponsors: Abbott, AbbVie, Janssen, Johnson & Johnson, Lilly, Otsuka. Previous data checks suggests that we should expect to obtain a pooled sample of ~31 000 participants from 77 studies provided on the Vivli platform (
Table 2).

**Table 1. T1:** Inclusion/exclusion criteria for selecting trials and participant data.

Variable	Inclusion criteria
Study Type	Randomized controlled multi-arm trial
Data Type	Individual Participant Data
Phase	II, IIa, IIb, III, IIIa, IIIb, and IV
Population/Diagnostic Criteria	Participants with Schizophrenia Spectrum Disorders, aged 18 years and older
Treatment	Antipsychotic medication
Comparator	*Placebo* (to establish efficacy) *Active Comparator* (to establish baseline psychometric model)
Active Comparator	*Primary* (standard) *:* first-generation vs second-generation antipsychotics (optionally adding D2 partial agonists as a third category where feasible). *Exploratory:* receptor-based taxonomy as proposed by McCutcheon et al. ^ 21 ^
Outcome	Positive and Negative Syndrome Scale (PANSS) and/or Brief Psychiatric Rating Scale (BPRS)
Covariates	Sex (if available: Age)
Moderator Variable	Sex Stage of illness (sensitivity analysis)
Timing of Outcome Assessment	6 weeks, as per Younis et al. ^ 22 ^/ *4 weeks for sensitivity analysis*

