	**Exclusion Criteria**
	All studies outside of the above parameters

**Table 2. T2:** Expected Sample.

Database One:		https://yoda.yale.edu/ (YODA Project)
Number of studies requested	-	62
Number of studies by sponsor		
*Janssen*	-	26
*Johnson & Johnson*	-	36

Database Two:		www.vivli.org (Vivli)
Number of studies requested	-	77 (62 are overlapping with YODA)
Number of studies by sponsor		
*Abbott*	-	1
*AbbVie*	-	1
*Lilly*	-	9
*Janssen*	-	26
*Johnson & Johnson*	-	36
*Otsuka Pharmaceuticals*	-	4

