### Stage 1: Establishing optimal psychometric models of PANSS and BPRS

### Exploratory and Factor analytic approaches

Data will be randomly split into exploratory and confirmatory datasets, as recommended by Lubke and Luningham,
^
27
^ with stratification by treatment group and trial to ensure balanced representation. For stratification and subsequent subgroup/invariance checks, active antipsychotic arms will be coded using literature-standard classification (primary approach: first-generation vs second-generation antipsychotics; where feasible, a third category for D2 partial agonists may be considered). In exploratory analyses, we will additionally code active agents using McCutcheon and colleagues’ data-driven receptor-based taxonomy,
^
21
^ namely muscarinic (M2-M5) receptor antagonists; dopamine (D2) partial agonists and adrenergic antagonists; serotonergic and dopaminergic antagonists; and dopaminergic antagonists. We will ascertain factor models of schizophrenia for baseline (pre-treatment), combined outcome (post-treatment; 6 weeks) and separately for placebo and treatment groups. We will further evaluate measurement invariance across major arm categories (e.g., placebo vs active treatment and, where supported, across active treatment-arm classes) within the best-fitting baseline model(s).

Parallel analysis will be applied to the exploratory datasets to determine symptom dimensionality.
^
28
^ Next, the EFA will be performed, using oblique rotation to allow for correlated symptom domains, to examine the factor structure of the exploratory dataset. Models will be refined iteratively by evaluating factor loadings below 0.3 and/or communalities below 0.4, with poorly performing items removed where justified to achieve stable and interpretable solutions.
^
29
^

In the confirmatory dataset, CFA will be used to formally test candidate psychometric models identified during the exploratory phase. In addition to simple structures derived from EFA, established alternative models, including higher-order and bifactor representations, will be evaluated.
^
30

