### Limitations

Several limitations should be acknowledged. Our planned analysis relies on available trials within controlled-access repositories: Hence, data might vary regarding follow-up timing, inclusion criteria, and data completeness, which may influence both psychometric models and effect size estimates. Psychometric BPRS and PANSS modelling across heterogeneous trials may yield more than one statistically defensible solution. We will therefore prioritise transparency in model comparison and report repository-specific results. Psychometric refinement may improve measurement in some contexts, but not in others. Data user agreements with Vivli and YODA Project may limit sharing of IPD and restrict reproducibility to code/scripts and permitted metadata, rather than full data transparency.

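### Results by repository are offered as a response to competing models, but as listed the YODA trials are a subset of the Vivli trials, so agreement between the two is largely built in

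*Protocol article*

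**What the plan says.** In the Discussion, under Limitations, the protocol article warns: "Psychometric BPRS and PANSS modelling across heterogeneous trials may yield more than one statistically defensible solution". The next sentence gives the response: "We will therefore prioritise transparency in model comparison and report repository-specific results". It does not define which trials make up each repository's results.

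Table 2 (Expected Sample) gives the counts. For YODA it has "Number of studies requested - 62", made up of 26 Janssen and 36 Johnson & Johnson studies. For Vivli it has "77 (62 are overlapping with YODA"), with the same 26 and 36 plus Abbott 1, AbbVie 1, Lilly 9 and Otsuka 4. The section on setting and eligibility adds: "Requested studies from the YODA Project are solely sponsored by Johnson & Johnson". The same section describes the expected data as a "pooled sample of ~31 000 participants from 77 studies provided on the Vivli platform".

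**The concern.** A reader who sees results for two repositories side by side will tend to treat them as two samples. Here the repository is mainly a route of access: YODA contributes no trial that Vivli lacks, and the Vivli total is the whole pooled data set. If the two columns are all 77 trials and 62 of those 77, similar factor structures, retained items or SMD differences would be expected even if the other 15 trials behaved quite differently.

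This matters for Stage 1 in particular. Roughly four fifths of the trials come from one sponsor group, so a model that suits those trials could be selected as the best PANSS or BPRS model, and the repository results would give little warning that it fits the rest poorly. The other checks described do not fill this gap:

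- The exploratory/confirmatory split ("Data will be randomly split into exploratory and confirmatory datasets") is stratified by trial, so both halves have the same mix of sources.
- Invariance is planned across arms and sex, and the network bootstrap assesses stability. Neither is described by data source.
- The sensitivity analyses concern week 4 against week 6 and illness stage.
- The trial-level SMDs can reveal heterogeneity in effects, but they use scores whose items are already fixed, so they do not show whether the same items would be retained.

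**Working it through.** **Inputs (Table 2).** Janssen and Johnson & Johnson are treated as one group, in line with the eligibility section.

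- YODA: 26 + 36 = 62, matching the stated 62.
- Vivli: 1 + 1 + 9 + 26 + 36 + 4 = 77, matching the stated 77.
- Vivli only: 1 + 1 + 9 + 4 = 15 = 77 − 62, matching the stated overlap.

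The overlap is 62/62 = 100% of YODA and 62/77 = 80.5% of Vivli.

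**Equal trial weights, nested reading (62 against all 77).** Let A be the mean over the 62 shared trials, B the mean over the 15 others, and V the mean over all 77.

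- V − A = (15/77) × (B − A), so the visible share of a true gap is 15/77 = 19.5%. For illustration, a gap of 0.10 SMD would appear as 0.10 × 15/77 = 0.019.
- Sampling correlation of A and V with equal trial variances: √(62/77) = 0.90.
- SD of the difference with trial variance 1: √(1/62 − 1/77) = 0.056. For independent sets of 62 and 77 it would be √(1/62 + 1/77) = 0.171. The nested difference therefore varies about 33% as much as one between separate samples.

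**On the plan's own scale.** The Discussion has in mind effect-size differences of roughly 10–15%. If refinement gained 15% in the 62 trials and nothing in the other 15, the two repository results would differ by 15 × 15/77 = 2.9 percentage points.

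**Unequal weights.** Participants per repository are not reported. Let s be the share held by the 15 Vivli-only trials, with precision proportional to participants. The correlation is then √(1 − s) and the visible share is s.

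| Assumed s | Correlation | Visible share of gap |
|---|---|---|
| 5% | 0.97 | 5% |
| 19.5% (equal weights) | 0.90 | 19.5% |
| 40% | 0.77 | 40% |

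**Disjoint reading (62 against 15).** No trial is shared, sampling errors are independent, and the whole gap is visible. The SE of the contrast with trial variance 1 is √(1/62 + 1/15) = 0.288.

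The disjoint split creates no new information about a mean SMD: 0.288 × 15/77 = 0.056, the nested SD. A reader who knew the weights could recover the gap by rescaling. No such rescaling exists for the retained item set or the choice of factor structure, which is where the response to competing models is needed.

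**The case against.** The strongest case against is that too much is being read into one reporting sentence. It stands in the Limitations and not in the statistical analysis plan, sets no replication criterion, and never says that agreement between repositories will count as confirmation. Table 2 discloses the overlap openly. The phrase could also mean the 62 shared trials against the 15 Vivli-only ones, which is already a disjoint comparison. The plan has other safeguards, and a pattern by sponsor in the SMD differences could be seen in the trial-level results.

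Most of this stands, and it limits the point. A reader might infer that the two sets of results must agree, or that the comparison can show nothing. The documents do not support that: the sets differ by 15 trials, the correlation is below 1, and the disjoint reading is open. A reader might also infer that the authors present this as a replication test, or as their only answer to heterogeneity; they do neither. Nor do the documents say that sponsors differ in how raters were trained or trials were run, so sponsor is proposed only as a practical way to form separate sets.

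What the objection does not remove is that the article ties repository reporting to the problem of several defensible models, leaves the sets undefined, and lists them as nested. None of the other checks described examines model structure by data source.

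**Conclusion.** The point holds as a moderate one about reporting. As listed, YODA against Vivli is a part-whole comparison in which agreement is largely built in: correlation about 0.90 and about one fifth of a true gap visible with equal trial weights, or 0.97 to 0.77 and 5% to 40% if the 15 other trials hold 5% to 40% of participants. These figures rest on the nested reading, on equal trial variances or precision proportional to participants, and on counts of studies requested. The share could differ in the placebo-controlled trials used for the primary comparison, which the article does not count by repository.

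The overlap should not be taken to mean that trials are counted twice. The pooled sample is described as 77 studies, each counted once, so the primary pooled estimate is unaffected.

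**What to change.** Keep the Stage 1 derivation on the pooled data. Replace the promise of repository-specific results with results for two mutually exclusive sets: the 62 Janssen/Johnson & Johnson trials and the 15 trials of other sponsors (Abbott 1, AbbVie 1, Lilly 9, Otsuka 4). For each set, report the fit of the chosen models, which items would be retained, and the Stage 2 SMD differences, where the data allow. State in the same sentence that all YODA trials are also held on Vivli.

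Deriving the scoring in the 62 trials alone and testing it in the 15 is not needed. It would change every abbreviated and weighted score and would base the models on a single sponsor group.

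The cost is a short change of text and a modest amount of further analysis, using the sponsor grouping already in Table 2. Intervals in the 15-trial set will be wider, and that set may hold few placebo-controlled or BPRS trials; the document does not say. Where it is too thin for a model to be fitted, reporting that plainly is enough.

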## Ethics and consent

Ethical approval for the planned study was granted for the data collection by the Royal College of Surgeons in Ireland Research Ethics Committee (HREC Reference Number: REC202506033). Consent was not required for this study because no data were collected or analysed for this manuscript. The planned analyses will use secondary data, and consent for the use of participants’ data in future research beyond the original study was obtained by the respective study sponsors.

## Generative AI statement

The author(s) declared that Generative AI was used in the creation of this manuscript. During the preparation of this work authors used ChatGPT (GPT-4o mini, OpenAI) to refine the draft wording as well as a free online version of DeepL Write in order to cross-check the English phrasing and grammar. After using these tools, the authors reviewed and edited the content as needed and take full responsibility for the content of the published article.

## Data Availability

The data management plan and documentation describing the trials included in this study are openly available through Zenodo (v1.0; DOI:
https://doi.org/10.5281/zenodo.19557064) and the Open Science Framework (v1.0;
https://osf.io/xf6ac/files/6nb8g). Access to the underlying study data was obtained via Vivli (
www.vivli.org) and the YODA Project (
https://yoda.yale.edu/). The IPD used are not openly shareable because they comprise anonymised personal data and are subject to legal, ethical, and contractual restrictions, including GDPR requirements, consent restrictions, data use agreements, and sponsor or platform terms. Access to these data may be requested through Vivli and the YODA Project, subject to their respective governance and access requirements. Openly shareable materials will be provided via Zenodo and OSF under an open licence. These materials include non-disclosive derived outputs, such as aggregate trial-level estimates, psychometric parameters where permitted, model fit indices, analysis code, documentation, and synthetic or example data. These resources provide transparency regarding the trial selection and the analyses underlying the findings reported in this article.
